### Sample size setting

2.7

The primary endpoint of this trial is progression-free survival (PFS). Progression is noted when patients experience either of the following events: A) Imaging with CT scan or MRI reveals local progression or distant metastasis (event occurrence date: date of the imaging) and B) The physician judges that ureteroscopic treatment cannot be completed in the follow-up ALA-PDD-assisted ureteroscopy (event occurrence date: date of the ureteroscopy). The date of the initial ALA-PDD-ULA is taken as the starting point. The historical data of the Department of Urology and Andrology, Kansai Medical University Hospital was obtained from consecutive patients undergoing ULA without PDD assistance. The 2-year progression-free survival (PFS) rate of ULA without PDD assistance and that with PDD assistance was 58% and 90%, respectively. The required sample size was determined to test our null hypothesis of superiority in the 2-year PFS rate after the initial surgery. Assuming that the threshold survival rate is 58% and expected survival rate is 90%, 14 patients are required with a 3-year registration period and 2-year tracking period years to provide 90% power (β = 0.10) and an α level of 0.05 (two-sided). Given the 20–30% proportion of ineligible patients, a total of 20 trial cases will be enroled in this study. We calculated the sample size using Statistical Tools 2019 provided by Cancer Research and Biostatistics (https://stattools.crab.org/).

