**Methods:**

The FLUAM trial is a prospective, single-center, single-arm pilot trial to investigate the efficacy of 5-aminolevulinic acid-mediated photodynamic diagnosis (ALA-PDD)-assisted ULA for localized UTUC and the usefulness of the UroVysion® assay (multiprobe fluorescence in situ hybridization) as a monitoring test after the kidney-sparing treatment. After the screening and registration, a total of 20 patients with localized UTUC will undergo the initial ALA-PDD-assisted ULA followed by the second look ALA-PDD-assisted ureteroscopic examination. The primary endpoint is progression-free survival. Secondary endpoints include patient reported outcomes, diagnostic accuracy of UroVysion assay to detect tumor recurrence, adverse events, and safety of the intervention.

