### Inclusion criteria

2.2

The flow chart, patient enrolment, endpoints of the FLUAM trial are depicted in Fig. 1. The trial design and protocol adhere to the Recommendations for Interventional Trials (SPIRIT) criteria [19]. The completed SPIRIT checklist can be found in Supplementary data. Investigators and patients will be aware of the intervention of oral administration of ALA. Patients will undergo a general work-up and radiographical examinations, including CT, CT-urography (CT-U) or MRI, cystoscopy, and urine cytology. Diagnostic ureteroscopy with biopsy ± upper urinary tract catheterization or irrigation cytology are performed to evaluate the tumor grade, tumor location, architecture, and feasibility of the ULA. Tumors are staged and graded according to the eighth edition of the American Joint Committee on Cancer (AJCC) TNM classification [20], by an experienced uropathologist ([name]). Prior to enrolment in this trial, patients must meet all of the following inclusion criteria:(i)Patients with clinical Ta–1N0M0 localized UTUC desire kidney-preservation therapy and meet any of the following A to E.A.Tumor develops in patients with solitary kidney or tumor develops bilaterally.B.Patients with chronic kidney disease are expected to avoid renal replacement therapy in the future by kidney-preservation therapy.C.Due to poor performance status, it is clinically judged that total RNU is not indicated.D.Patients have a single tumor with a major axis of 10 mm or less and have a healthy kidney on the contralateral side.E.Patients desire kidney-preservation therapy, although they are recommended RNU.(ii)Age, 20 years or older (regardless of gender)(iii)The pathological diagnosis is confirmed by ureteroscopic biopsy.(iv)The name and disease status have been informed to the patient, and he/she must be given an explanation when participating in this study. The written consent at his/her must be obtained with sufficient understanding.(v)Bone marrow function and organ function (excluding renal function) are sufficient by the following laboratory findings within 60 days:A.Hemoglobin ≥9.0 g/dL (no transfusion within 4 weeks)B.White blood cell count, the lower limit to 12,000/mm^3^C.Neutrophil count ≥2,000/mm^3^D.Platelet count ≥100,000/mm^3^E.Total bilirubin ≤2 × the upper limit of normalF.Aspartate aminotransferase (AST) ≤ 2 × the upper limit of normalG.Alanine aminotransferase (ALT) ≤ 2 × the upper limit of normal

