### Follow-up schedule and data collection

2.6

Patient data will be collected before and after the surgery; 1, 3, 6, 9, 12, 15, 18, 21, 24, and 27 months after the initial ALA-PDD-ULA; and at the end of the trial (Fig. 3). To improve monitoring adherence, the clinician will take time to explain the need for post-operative surveillance examination, including second-look URS, and encourage the participants to undergo routine cystoscopy, urine cytology, and CT/CT-U/MRI. The assessment includes patient-reported outcomes, such as the SF-8™, EORTC QLQ-C30, FACT-BL, International Prostate Symptom Score (IPSS), and overactive bladder symptom score (OABSS). The postoperative observational evaluation such as PROs can be discontinued upon participant request. The data will be documented in specific Case Report Forms for complete blood count, serum chemistry, cystoscopy, urine cytology, CT/CT-U/MRI, genitourinary adverse events (AEs), and other possible AEs using the Common Toxicity Criteria for Adverse Events (CTCAE v 5.0). When recurrence is suspected in imaging examinations, ALA-PDD-ureteroscopy is considered and, if recurrent tumor is present, ALA-PDD-ULA is additionally performed. AEs strongly related to the intervention of ALA-PDD-ULA are listed as follows: “Intraoperative urinary injury,” “Urinary tract infection,” “Fever,” “Renal hemorrhage,” “Hematuria,” “Creatinine increased”, “Urinary frequency”, “Photosensitivity”, “Hepatobiliary disorders”, “Urinary tract pain”, “Urinary urgency”, and “Dysuria”. Any other potential AEs are recorded and grouped into ‘related AEs’ or ‘unrelated AEs.’ When serious AEs occur, investigators report to the Safety Monitoring Committee.

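### Event B covers only follow-up ureteroscopy and nephroureterectomy is not listed, so patients who leave the ureteroscopic pathway for upper-tract tumour without meeting event A or B are not counted as failures

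*Protocol article*

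**What the plan says.** The primary endpoint is defined in the protocol article, section 2.7 (Sample size setting). The list is closed: "Progression is noted when patients experience either of the following events". Event A is "Imaging with CT scan or MRI reveals local progression or distant metastasis", dated at the imaging. Event B is the physician's judgement that "ureteroscopic treatment cannot be completed in the follow-up ALA-PDD-assisted ureteroscopy", dated at that ureteroscopy. On the time origin: "The date of the initial ALA-PDD-ULA is taken as the starting point".

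Four other places bear on which patients the list reaches:

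- **Abstract, Methods.** All 20 patients are to "undergo the initial ALA-PDD-assisted ULA followed by the second look ALA-PDD-assisted ureteroscopic examination".
- **Section 2.6 (Follow-up schedule and data collection).** For later procedures: "When recurrence is suspected in imaging examinations, ALA-PDD-ureteroscopy is considered". The legend of Fig. 3 likewise ties repeat ablation after 6 months to suspicious imaging.
- **Section 2.2 (Inclusion criteria), (i)E.** One route of entry is: "Patients desire kidney-preservation therapy, although they are recommended RNU".
- **Section 2.10 (Statistical analysis).** Superiority is concluded if the lower 95% limit of the two-year PFS rate, with Greenwood's variance, exceeds 58%. The only competing event named is death from other causes.

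Nowhere does the article make nephroureterectomy an event, a competing event or a censoring point.

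**The concern.** Time at risk begins at the first ablation, but the procedural event can occur only at a later one. If the tumour cannot be cleared at the first ablation and the patient goes to nephroureterectomy before the second look, neither A nor B is met. The same holds for a patient who converts later without imaging progression and without another ureteroscopy. Once that kidney and ureter are gone, B can no longer occur on that side.

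These are failures of the approach under test: the Introduction states the aim as less recurrence and progression through complete resection. The decision compares one arm with a fixed external rate, so no concurrent control shares the undercount. In a trial of 20, each such patient is worth 5 percentage points (1/20).

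**Working it through.** **1. The plan's own figures.** Inputs from section 2.7: 58% against 90% at two years, two-sided 0.05, 90% power, 3 years of accrual, 2 years of follow-up. Assume exponential survival:

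- hazards: λ0 = −ln(0.58)/2 = 0.2724 and λ1 = −ln(0.90)/2 = 0.0527
- probability of an event under the alternative, uniform accrual: 0.1675
- cube-root hazard scale: n = (1.960 + 1.282)² × λ1^(2/3) / [9 × 0.1675 × (λ0^(1/3) − λ1^(1/3))²] = 13.1, so 14
- inflation: 14/(1 − 0.30) = 20

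Both stated numbers reproduce, although the article does not say which formula its tool uses. The point below does not depend on this calculation.

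**2. Which patients the list misses.**

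| Course | Counted? |
|---|---|
| Imaging progression, then conversion | Yes, A at the imaging date |
| Incomplete first ablation, treatment cannot be completed at the second look | Yes, B |
| Leaves the pathway for upper-tract tumour before the second look, no imaging progression | No |
| Converts later, no imaging progression, no further ureteroscopy | No |

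**3. Effect of one patient on the decision.** Complete two-year follow-up, so Greenwood's variance reduces to p(1 − p)/n; plain limit = p − 1.96 × √[p(1 − p)/n].

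| Progression-free | Estimate | Lower limit | Above 58%? |
|---|---|---|---|
| 17/20 | 85.0% | 69.4% | yes |
| 16/20 | 80.0% | 62.5% | yes |
| 15/20 | 75.0% | 56.0% | no |
| 12/14 | 85.7% | 67.4% | yes |
| 11/14 | 78.6% | 57.1% | no |

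Suppose 20 patients have four counted events and one missed failure:

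- counted as an event: 15/20, limit 56.0%, not superior
- kept event-free: 16/20, limit 62.5%, superior
- censored before any event: 15/19 = 78.9%, limit 0.789 − 1.96 × √(0.789 × 0.211/19) = 60.6%, superior

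Censoring therefore does not remove the problem.

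**4. False-positive rate, n = 20.** Let the true failure-free rate be 58%. If one or two patients per 20 have failures that the definition misses, the apparent rate is 63% or 68%. These frequencies are assumptions. With X ~ Binomial(20, p):

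| Interval | Needed | p = 0.58 | p = 0.63 | p = 0.68 |
|---|---|---|---|---|
| Plain | X ≥ 16 | 3.5% | 8.6% | 18.3% |
| Log-log | X ≥ 17 | 1.0% | 3.0% | 7.7% |

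The log-log cut-off follows from limits of 60.4% at 17/20 and 55.1% at 16/20. Section 2.10 names Greenwood's variance but not the scale of the interval, so both are shown. On the log scale, 15/20 would also pass (58.2%).

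**The case against.** The strongest case against is that few patients can fall into the gap. A second look is planned for everyone and section 2.6 has clinicians encourage attendance, so residual tumour after an incomplete first ablation normally meets an event-B assessment. Later conversions tend to start from suspicious imaging, and some will already be event A. Diagnostic ureteroscopy checks feasibility before enrolment (section 2.2), and ablation continues until no PDD-positive tumour remains (section 2.5). Patients entering under (i)E chose kidney preservation against advice, so early conversion is possible but not shown to be likely. All of this stands, and it limits the point to patients who leave the pathway as described.

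A reader might infer that follow-up ureteroscopy is optional throughout. The documents do not support that: the conditional wording in section 2.6 covers later ureteroscopy after suspicious imaging, not the second look. A reader might also infer that any failed first ablation is scored as progression-free. That fails for the same reason; moreover, no censoring rule is shown, so a missed patient may be censored instead.

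Censoring rules and the handling of subsequent treatment are commonly left to the full protocol or analysis plan, so their absence here is not the finding. The finding is what the stated event list fixes: it is closed, and B is confined to follow-up.

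**Conclusion.** The point holds in limited form. As worded, the definition leaves some failures of ureteroscopic management uncounted, and whether those patients stay event-free or are informatively censored, two-year PFS is biased upward.

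The size cannot be determined from the article, because the number of such patients is not given. The rise from 3.5% to 8.6% or 18.3% (1.0% to 3.0% or 7.7% on the log-log scale) is an illustration. It rests on one or two missed failures per 20, all 20 patients analysed with complete follow-up, and a historical 58% that counts such failures. The article does not say how that series was coded. If it used the same A/B list, the comparison would be like for like and this inflation would not follow. The firmer result is that one patient can reverse the conclusion, at 20 or at 14 patients analysed with the plain limit.

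**What to change.** In section 2.7, word event B to cover the initial or any follow-up ALA-PDD-assisted ureteroscopy. Add as an event nephroureterectomy, or other definitive treatment that replaces ureteroscopic management, when given for upper-tract tumour, dated on the day of that treatment. This changes only how outcomes are counted, not how patients are managed.

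Check that the 58% historical series uses the same definition. If it cannot be re-coded, keep the A/B definition as primary and report the broader one beside it as a pre-specified sensitivity analysis in section 2.10. Agreement between the two need not be a condition for claiming superiority.

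The cost is a change of wording, coding of treatment dates and a check of the historical definition. The PFS estimate may be slightly lower. The sample size need not change.

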### Statistical analysis

2.10

Descriptive statistics will be computed for all study variables. EZR 1.54 (Saitama Medical Center, Jichi Medical University, 2020) and PRISM software version 7.00 (GraphPad Software, Inc., San Diego, CA, USA) were used for statistical analyses and data plotting, respectively. A two-sided P value of less than 0.05 will be considered to be statistically significant.

The full analysis set population and the per protocol set population will be separately analyzed for both the primary endpoint (two-year PFS rate) and survival outcomes listed in the secondary endpoints (Fig. 1). The per-protocol set population will be analyzed for the other secondary endpoints. The PFS of study population will be estimated by Kaplan Meier method, and 95% confidence interval (CI) will be calculated using Greenwood's formula for variance. When the lower limit of 95%CI of two-year PFS rate is more than 58% (threshold survival rate), the ALA-PDD-ULA is considered superior to the conventional ULA without PDD assistance. When the lower limit of 95%CI of two-year PFS rate is 58% or less, the ALA-PDD-ULA is considered not superior to the conventional ULA without PDD assistance. In addition, a sensitivity analysis of the primary endpoint will be performed using the Fine-Gray subdistribution hazard regression. This model considers patients who die of other causes (competing events) before recurrence or progression.

The amount of change in other post-operative observations over time will be analyzed using the repeated measures analysis of variance, Wilcoxon signed-rank sum test, or Mann-Whitney *U* test as appropriate. Mixed-effects models for repeated measures will be applied to detect multiple change-points in longitudinal data. To evaluate the diagnostic accuracy of UroVysion test, the result is compared to the pathological diagnosis obtained by URS biopsy. The sensitivity, specificity, positive predictive value, negative predictive value, and diagnostic accuracy are determined according to standard methods [23]. The sensitivities of UroVysion test and the combination with the conventional cytology are compared to that of conventional cytology alone using McNemar's test.

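### The stated 90% power with 14 patients at two-sided alpha 0.05 is not delivered by the planned 24-month Kaplan-Meier rule, and the formula behind 14 is not given

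*Protocol article*

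**What the plan says.** Protocol article, section 2.7 (Sample size setting), frames the calculation as one "to test our null hypothesis of superiority in the 2-year PFS rate after the initial surgery". The inputs are a 58% threshold and a 90% expected rate ("Assuming that the threshold survival rate is 58% and expected survival rate is 90"%). The result is "14 patients are required with a 3-year registration period and 2-year tracking period", and this is said "to provide 90% power (β = 0.10) and an α level of 0.05 (two-sided"). Enrolment follows from that figure: "Given the 20–30% proportion of ineligible patients, a total of 20 trial cases will be enroled in this study". The section names the software but not the test, formula or transformation.

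Section 2.10 (Statistical analysis) fixes the decision. PFS is estimated by Kaplan-Meier with a Greenwood 95% interval, and superiority is declared "When the lower limit of 95%CI of two-year PFS rate is more than 58% (threshold survival rate"). The scale of the interval (plain, log or log-log) is not stated. The primary endpoint is analysed in both the full analysis set and the per-protocol set.

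**The concern.** Power belongs to a decision rule. The rule here reads one number, the lower 95% limit at 24 months, so it tests at a nominal one-sided 2.5%. Section 2.7 attaches 90% power to 14 patients for the two-year rate, but a direct calculation for that rate at two-sided 0.05 does not give 14.

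The consequence lies in how a negative result is read. Section 2.10 calls the technique not superior if the limit is 58% or less. If the true two-year rate is 90%, section 2.7 implies that this happens one time in ten. With 14 patients it happens in 15.8% of trials (100 − 84.2) on plain limits and 41.5% (100 − 58.5) on log-log limits. A reader would also not know which of these applies, because the scale is open.

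**Working it through.** **Inputs.** Threshold p0 = 0.58, expected p1 = 0.90, two-sided alpha 0.05, power 90%, 3-year accrual, 2-year tracking, n = 14, 20 enrolled, 20–30% ineligible (all section 2.7). The rule is from section 2.10. Assumption: every patient is observed to 24 months, so the Kaplan-Meier estimate is (n − x)/n with x progressions.

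**Step 1: where 14 could come from.** One-sample normal approximation: n = [(z_a·√(0.58×0.42) + 1.2816·√(0.90×0.10)) / 0.32]².
- One-sided 0.05 (z_a = 1.645): 13.98, so 14.
- Two-sided 0.05 (z_a = 1.960): 17.85, so 18.

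Exponential models with the stated accrual and tracking use hazards −ln(0.58)/2 = 0.272 and −ln(0.90)/2 = 0.0527 per year. The event probabilities are then 0.604 and 0.168. Two-sided 0.05 gives:
- log-hazard scale 11.8;
- cube-root scale 11.7, or 13.1 (so 14) with the alternative variance only;
- hazard scale 15.04.

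Other parametric variants scatter more widely. So 14 can be reached one-sided by a landmark formula, or two-sided by a survival model.

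**Step 2: every possible cut-off at n = 14.** Error is P(X ≤ c) for Binomial(14, 0.42); power is P(X ≤ c) for Binomial(14, 0.10).

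| Success if progressions ≤ c | One-sided error | Power | Interval that gives this cut-off |
|---|---|---|---|
| 1 | 0.5% | 58.5% | log-log Greenwood; exact |
| 2 | 2.9% | 84.2% | plain Greenwood |
| 3 | 9.6% | 95.6% | log-scale Greenwood |

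For example, the plain lower limit is 0.674 with 2 progressions and 0.571 with 3. The log-log limit is 0.591 with 1 and 0.539 with 2. No cut-off gives 90% power with error at or below 2.5%, so no choice of interval can.

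**Step 3: other numbers of patients.** Of 20 enrolled, 30% or 20% ineligible leaves 14 or 16; 14/0.7 = 20 reproduces the enrolment figure. Each cell gives cut-off, power and one-sided error.

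| n | Plain Greenwood | Log-log Greenwood | Exact (Clopper-Pearson) |
|---|---|---|---|
| 14 | ≤2, 84.2%, 2.9% | ≤1, 58.5%, 0.5% | ≤1, 58.5%, 0.5% |
| 15 | ≤3, 94.4%, 6.8% | ≤1, 54.9%, 0.3% | ≤2, 81.6%, 1.9% |
| 16 | ≤3, 93.2%, 4.7% | ≤2, 78.9%, 1.2% | ≤2, 78.9%, 1.2% |
| 18 | ≤4, 97.2%, 6.9% | ≤2, 73.4%, 0.5% | ≤3, 90.2%, 2.2% |
| 20 | ≤4, 95.7%, 3.5% | ≤3, 86.7%, 1.0% | ≤3, 86.7%, 1.0% |

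Zero progressions is counted as a success throughout, although Greenwood's variance is then zero. Plain limits pass 90% power from n = 15 on only because their error exceeds 2.5%.

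**The case against.** The strongest defence is that 14 may be a correct two-sided result. Accrual and tracking periods are not used by a fixed-landmark formula, but they are inputs to a survival-model calculation. Such models give figures around 14. In simulation, a two-sided 5% exponential-model test with 14 patients has about 95% power at a one-sided error of about 2.2%. This stands against a reading that Step 1 invites: that a one-sided alpha was used and mislabelled as two-sided. The match to 13.98 is numerical only. The document does not show the formula, so a sidedness error is not established.

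The defence does not rescue the stated power. A parametric test draws on follow-up from year 2 to year 5, whereas the rule in section 2.10 uses nothing after 24 months. If 14 came from such a model, the trial was sized for a test it will not perform.

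Two further points are fair. A range of 58% to 82% for 14–16 patients might be taken as the power of the trial, but it holds only for exact limits, which section 2.10 does not name. And if all 20 patients enter the full analysis set, exact power is 86.7%, close to the target.

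The article also calls the study a pilot, and nowhere says that a negative result carries 90% assurance. That lowers the stakes but does not make the power statement correct. Nor is this detail left to a fuller document: the article itself states the number, alpha, power, both rates and the rule, and they do not fit together.

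**Conclusion.** The point holds as a mismatch between sample size and decision rule. For the rule in section 2.10, 14 patients give 58.5% to 84.2% power on log-log or plain limits, or 95.6% at the price of a 9.6% one-sided error. The stated combination of 90% power and two-sided 0.05 is not a property of this design under any interval. A landmark calculation at two-sided 0.05 gives 18 by normal approximation, and 18 is also enough with exact limits. The origin of 14 remains open.

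The figures assume the plan's own 58% and 90% and complete observation to 24 months. Section 2.10 itself foresees deaths from other causes before progression. Loss before 24 months would lower power further. The size of the problem also depends on which set is read: 20 patients in the full analysis set lose little against the target, whereas 14 to 16 evaluable patients can lose much.

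**What to change.** Change the two sections together; no extra enrolment is needed.

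1. **Section 2.10:** name one interval that keeps the one-sided error at or below 2.5%. Examples are the exact (Clopper-Pearson) interval when all patients reach 24 months, or log-log Greenwood if there is censoring.
2. **Section 2.7:** name the formula, match it to that rule and restate power. With exact limits, 18 evaluable patients give 90.2% (success with at most 3 progressions, error 2.2%). All 20 in the full analysis set give 86.7% (at most 3, error 1.0%). If 14, 15 or 16 remain, power is 58.5%, 81.6% or 78.9%. With log-log Greenwood, power is 58.5%, 54.9%, 78.9% and 86.7% at 14, 15, 16 and 20.

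The statement about 18 patients and at most 3 progressions must not go into section 2.7 alone. Under plain Greenwood the cut-off at 18 is 4 progressions (error 6.9%), and under log-log it is 2 (power 73.4%), so a new contradiction would arise.

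The cost is wording in two sections and a stated power that is less favourable than 90% for the numbers the plan expects.
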